### Data collection and management

After meeting all inclusion criteria and agreeing to participate, participants will be coded with a study number and all data referring to the patient will be recorded by this number rather than by name. Patients undergo routine preoperative laboratory and imaging assessments, including a review of preoperative medication and documentation of preoperative opioid use. A Case Report Form (CRF) will be used to collect information from participants, including baseline information, imaging results and follow-up visits. Shoulder mobility, clinical and demographic data, pain scores, and shoulder mobility scores will be collected at follow-up points. Data will also be collected on complications and adverse reactions, including death, reinfection, reoperation, medical complications, rash or allergic reactions. Independent researchers will manually enter the raw data storage. A Data Security Monitoring Board (DSMB) has been set up to review the reliability and security of the data. CRF as well as uploaded data will be stored in a secure cabinet or password-protected folder respectively. Access to study data by other researchers will be restricted. No interim analysis is planned for topical application of 5% lidocaine as the safety concerns are minimal unless required by the Steering Committee or DSMB because of safety concerns.

Acute pain after ARCR is a concern for patients. In addition, a close follow-up and telemedicine will be performed to reduce the rate of loss to follow-up. All patients will be followed up for 3 months for postoperative recovery and monitoring of complications. Patients will receive a text message or email two days before each postoperative follow-up point.

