**Methods:**

In this randomized, double-blind, and placebo-controlled clinical trial, a total of 102 postoperative patients undergoing ARCR will be randomly assigned to either the LP5 group, receiving topical lidocaine analgesia, or the placebo control group. The primary outcome measure will be the change in the American Shoulder Elbow Surgeons score from pre-operation to 90 days post-operation. Secondary outcomes will include pain scores, range of motion, opioid use, safety indicators, blinding assessment and several shoulder function score questionnaires. The effect of the allocated treatment will be assessed at preoperative baseline and at 7-, 14-, 30- and 90-day postoperatively.

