**Discussion:**

In this study, the efficacy and safety of the 5% lidocaine patch will be evaluated in terms of short-term clinical symptoms in patients undergoing ARCR. The results of this study will help determine whether LP5 is effective in early functional recovery in ARCR and whether it relieves pain and reduces opioid consumption.

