### Eligibility

All patients confirmed with rotator cuff tear by MRI with symptoms (pain and/or weakness) and are failed to conservative treatments will be included. The exclusion criteria are (1) history of allergy to lidocaine or adhesive, (2) other significant organ disorders or substance abuse, (3) clear radiographic evidence of osteoarthritis of the glenohumeral joint, (4) presence of inflammatory arthritis including rheumatoid, (5) a history of ipsilateral shoulder dislocation or surgery, (6) irreparable tears, (7) pregnancy or heart disease, and (8) inability to understand questionnaires or express the level of pain.

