### Randomization and blinding

Prior to the start of the study, randomization will be performed using a computer-generated table of random numbers by the research pharmacy not involved in the screening of subjects. Included participants will be randomly assigned with a 1:1 allocation to either the lidocaine or placebo group, with each patient having an equal probability of being assigned to either the experimental treatment group or the placebo group. The material, size and colour of the placebo patch will be similar to LP5 as far as possible. Patients will use the patches under the guidance of their surgeons. The group allocation protocols will be enclosed in opaque envelopes to ensure blinding of the investigators, patients, and data analysts. These envelopes will be sealed and could only be opened after the study is completed.

If a subject experiences a serious adverse event or requires emergency resuscitation during the trial, whether or not it is related to the intervention, the intervention received by the subject will be disclosed. Subjects who disclose the intervention will be considered as drop-out cases. If the intervention is disclosed for more than 20% of participants, the trial will not be considered double-blind.

In addition, the allocation scheme of the intervention will be confidential to the evaluators collecting outcome data throughout the study. The statistical analysts will also not know whether participants are in the LP5 or placebo group until the statistical analysis is completed.

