**Safety assessments**							
**BRE**		×					×
**URT**		×					×
**LFTs**		×					×
**ESR**		×					×
**ASO**		×					×
**RF**		×					×
**Opioid consumption**		×	×	×	×	×	×
**Adverse events**		×	×	×	×	×	×

*Abbreviations*: *LP5* 5% Lidocaine patch, *ASES* American Shoulder and Elbow Surgeons, *OSS* Oxford Shoulder Score, *CMS* Constant-Murley, *PSQI* Pittsburgh Sleep Quality Index, *SF-36* 36-Item Short Form Survey, *VAS* Visual analogue scale, *PPT* Pressure pain threshold, *BRE* Blood routine examination, *URT* Urine routine test, *LFTs* Liver function tests, *ESR* Erythrocyte sedimentation rate, *ASO* Anti-streptococcus hemolysinv, *RF* Rheumatoid factor

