### Statistical analysis

The final data will be entered and counted by a professional statistician using SPSS 26.0 (IBM, Armonk, NY, USA). For continuous variables, the normality of measured data distributions will be evaluated using the Shapiro-Wilk test. Measurements will be expressed as mean ± standard deviation, if the data are normally distributed with uniform variance. Paired *t*-tests will be used for within-group comparisons before and after treatment, and independent samples *t*-tests will be used for between-group comparisons before and after treatment. If the data do not conform to a normal distribution or have an uneven variance, the measurement data will be expressed as median (interquartile range) [M(Q)] and the Wilcoxon rank sum test will be used for the analysis of the data before and after treatment. For categorical variables, chi-square tests or Fisher’s exact tests will be used to examine differences between groups and to describe effect sizes in terms of percentages and frequencies. Prior to any analysis, the pattern and reasons for missing data patterns will be investigated. The primary analysis will be conducted as an intention-to-treat analysis, which includes all participants with missing outcome data, unless there is clear evidence that its underlying assumption is inappropriate. Multivariable imputation by chained equations method will be used to impute missing data for the sensitivity analysis for the primary and secondary outcomes. *P*<0.05 indicates that the threshold of statistical significance has been reached.

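### The opioid-consumption comparison does not use the preoperative opioid use the trial records, which costs precision and makes a result harder to read if the arms differ in prior users

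*Protocol article*

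**What the plan says.** - **Eligibility.** The one exclusion that touches opioids is "other significant organ disorders or substance abuse". Prescribed opioid use is not excluded, and no washout is required.
- **Data collection and management.** Patients have a preoperative assessment "including a review of preoperative medication and documentation of preoperative opioid use".
- **Table 1.** The row "Opioid consumption" sits under safety assessments and is marked at baseline and at days 1, 7, 14, 30 and 90.
- **Abstract, Methods.** Opioid use is a secondary outcome: "Secondary outcomes will include pain scores, range of motion, opioid use, safety indicators".
- **Abstract, Discussion.** The trial is meant to show "whether it relieves pain and reduces opioid consumption". The main Discussion repeats the opioid question.
- **Randomization and blinding.** "Included participants will be randomly assigned with a 1:1 allocation to either the lidocaine or placebo group". The list is a computer-generated random number table. The section is silent on stratification.
- **Statistical analysis.** For continuous variables, "independent samples *t*-tests will be used for between-group comparisons before and after treatment". Wilcoxon rank sum is the fallback when data are non-normal or variances unequal. Paired t-tests are planned within groups. No covariate is named.

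**The concern.** Entrants have symptomatic tears that conservative treatment has not resolved, so some may already be taking prescribed opioids. In such a patient, postoperative intake mixes continued prior use with intake for surgical pain. The tests named in the plan treat the two alike.

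Two things follow. Differences between prior users and non-users stay in the error term of the opioid comparison, which the trial is not sized for (the sample size rests on ASES). And if one arm happens to receive more prior users, part of the observed difference reflects that allocation, with nothing in the named analysis to separate it from a patch effect. A baseline value that would deal with both is already collected.

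**Working it through.** **The plan's own figure.** There is none to reproduce: the protocol gives no prevalence of prior use, no consumption mean and no SD for opioid intake. The only document input is 51 per group (Sample size calculation).

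**Assumptions (not in the documents).** Share of prior users p = 0.10, 0.20, 0.30. Prior users consume r = 2 or 3 times what non-users do. Coefficient of variation (CV) within each stratum is 0.7, so its square is 0.49. The non-user mean is set to 1.

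**Step 1: variance explained by prior use.**

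Between strata: B = p(1−p)(r−1)². Within strata: W = 0.49[(1−p) + p·r²]. Share = B/(B+W).

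Example, p = 0.10, r = 2: B = 0.09; W = 0.49 × 1.30 = 0.637; share = 0.09/0.727 = 0.124.

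Example, p = 0.30, r = 3: B = 0.84; W = 0.49 × 3.40 = 1.666; share = 0.84/2.506 = 0.335.

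Removing that share shrinks the standard error (SE) by a factor of about √(1 − share): √0.876 = 0.94 to √0.665 = 0.82, a reduction of roughly 6–18%.

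**Step 2: how often the arms differ.** With independent Binomial(51, p) counts, the chance that the arms differ by 5 or more prior users (5/51 = 9.8 points) is 13.5%, 26.4% and 33.0% for p = 0.10, 0.20 and 0.30.

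**Step 3: what a 5-patient difference does.** Shift relative to the overall mean = (5/51)(r−1)/[1 + p(r−1)]. SE of the between-arm difference, on the same scale = √(B+W)/[1 + p(r−1)] × √(2/51), where √(2/51) = 0.198.

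| p | r | Variance share | Shift | SE | Shift/SE |
|---|---|---|---|---|---|
| 0.10 | 2 | 12% | 8.9% | 15.3% | 0.58 |
| 0.10 | 3 | 29% | 16.3% | 18.4% | 0.89 |
| 0.20 | 2 | 17% | 8.2% | 16.0% | 0.51 |
| 0.20 | 3 | 33% | 14.0% | 19.6% | 0.72 |
| 0.30 | 2 | 18% | 7.5% | 16.3% | 0.46 |
| 0.30 | 3 | 34% | 12.3% | 19.6% | 0.63 |

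The shift is below one standard error in every row.

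**Step 4: error rate and power.** A simulation used 20,000 trials per scenario, 41 per arm (the calculated group size before the drop-out allowance), normal outcomes with equal SD, 10–30% prior users, and prior users 0.5–2 within-stratum SD higher. This outcome model differs from the ratio model above, so the two sets of figures should not be combined.

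| | Unadjusted | Adjusted for prior use |
|---|---|---|
| Type I error, all trials | 4.9–5.3% | 4.7–5.4% |
| Type I error, arms differing by at least 15 points | about 6–25% | about 4–7% |
| Power, assumed 0.6 SD effect | 50–76% | about 76% |

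An imbalance of at least 15 points is uncommon: about 1%, 6% and 10% of trials at p = 0.10, 0.20 and 0.30 with 51 per arm.

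**The case against.** **Randomisation already covers this.** A reader might infer that chance imbalance in prior users biases the opioid comparison or inflates its false-positive rate. It does not. The two-sided 5% test allows for chance imbalance, and overall type I error stays near 5% without adjustment. Nor could a 5-patient difference by itself give a significant result, since it moves the estimate by less than one standard error. This part of the objection stands in full. It leaves lost precision, and error conditional on a marked imbalance.

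**The size is assumed.** Also true. Recording preoperative opioid use within a routine work-up does not show that many patients will have any, and if few do the point nearly disappears. The mean-shift and variance-share figures also describe a comparison of means, not the rank test the plan would use for skewed data.

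**Adjustment belongs in an analysis plan.** Often so, and the article does not rule it out. But Statistical analysis goes further than silence: it names the between-group tests, and they are unadjusted. An analysis plan that followed it would carry the same weakness.

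**The baseline value is not ignored.** It would be wrong to say it goes unused. The plan compares the groups before treatment and makes paired comparisons within groups, so an imbalance would be visible. Neither step corrects the postoperative contrast.

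**Allocation.** A reader might also take allocation to be unstratified. The article does not say so; it simply does not mention stratification.

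**Conclusion.** The point holds as a matter of efficiency and interpretation. Prior users are eligible, their use is recorded, opioid reduction is a stated question, and the named between-group tests leave the recorded value out. Under the assumed 10–30% prevalence, 2–3-fold consumption and within-stratum CV of 0.7, about 12–34% of the outcome variance is left in the error term. If the arms happen to differ noticeably in prior users, readers will have no pre-specified adjusted estimate to turn to.

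The documents do not support the stronger claim that the opioid conclusion would be biased or invalid. The real size depends on prevalence and consumption figures that the documents do not give. The outcome is secondary, so the primary ASES analysis is unaffected.

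**What to change.** Add one sentence to Statistical analysis: the between-group comparison of postoperative opioid consumption will be adjusted for documented preoperative opioid use (yes/no, or the baseline amount from Table 1) by ANCOVA or another regression model, and by a rank test stratified on preoperative use where the plan would otherwise switch to Wilcoxon. Choose the form of the covariate before unblinding, so that the choice between adjusted and unadjusted results cannot depend on the data.

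A comparison restricted to participants with no preoperative opioid use may be reported as well, but it is optional and supportive only. Eligibility can stay as it is.

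The cost is small: the variable is already collected, so there are no extra patients, visits or procedures. The downside is a model or stratified test in place of a simple two-sample test.

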### Oversight and monitoring

For this single-centre trial, the trial staff has trained investigators who are responsible for assessing the subgroups and clinical data collection. Providing oversight and guidance for this trial is the Quality Management Office of the First Affiliated Hospital of Soochow University, who will review the data and check the progress of the study.

### Quality control

Prior to the trial, all staff will be required to attend a series of training sessions. These sessions will ensure that relevant staff fully understands the study protocol and the standard operating procedures of the study. In order to maintain the consistently high quality of clinical trials, the Clinical Research Centre of the First Hospital of Soochow University will regularly monitor study files, informed consent forms, case report forms (CRFs), serious AEs and data records.

### Adverse event management

Any adverse events (AEs) occurring to participants during the clinical trial, whether or not they are related to the intervention, will be assessed and recorded at any time. Adverse events will be recorded on a designated Clinical Case Observation Form (CRF) Adverse Event Form and classified according to the Medical Dictionary of Regulatory Activities (MedDRA). During this period, if the participant feels a slight burning, tingling, redness, blistering or breakage of the local skin, the area will be disinfected and covered with sterile gauze to prevent infection. Other side effects caused by lidocaine such as: hypotension, dizziness, slowed heart rate and gastrointestinal reactions will be recorded on the CRF. Drug safety will be assessed by blood routine examination (BRE), urine routine test (URT), liver function tests (LFTs) and other indicators of significant organ damage. Indicators of joint cavity infection such as erythrocyte sedimentation rate (ESR), anti-streptococcus hemolysinv (ASO) and rheumatoid factor (RF) will be recorded. Data will be collected on complications and adverse reactions, including death, reinfection, reoperation, medical complications, rash or allergic reactions. Serious adverse events (SAEs) will have to be reported to the Ethics Committee of the First Affiliated Hospital of Soochow University within 24 h. In the event of a medical emergency, random coding and group allocation of individuals can be determined through standard operating procedures. These complications will be included in the secondary outcome of this study.

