### Intervention

The group allocation protocol will be performed prior to the procedure. Based on the random number, a pre-prepared opaque envelope containing either 5% LP measuring 14 × 10 cm^2^ and containing 700 mg of lidocaine or placebo patches was allocated to the patient. There is no difference between the placebo patches and LP5 patch in appearance or structure, but the placebo does not contain lidocaine. The patch will be divided into strips and applied around the shoulder crest immediately after surgery. The patch will be replaced with a new one every 12 h until 2 weeks postoperatively. Patients, test site medical staff and investigators were blinded to group allocation. In cases of severe shoulder pain, painkillers will be allowed as emergency medication and should be documented in the medical record. Patients will also be asked to record the name, dose, date, frequency and exact time of medication used and to report to the researcher if they have taken any medication during the study. Patient compliance will be maintained and monitored through good communication and constant reminders between medical staff and patients. Although patients will be advised to adhere to the protocol, it is not possible to fully exclude those patients who independently decide to undergo and not report other treatments or measures. We will explain in detail to the patients and their family members simultaneously. A close follow-up and telemedicine will be performed during the trial.

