### Outcomes measurement

Participants will be scheduled for a 3-month follow-up, with data collected at baseline (pre-operative), 1-, 7-, 14-, 30- and 90-day postoperative using a uniform standardized case report form. Baseline clinical data will be collected including age, gender, dominant hand, affected limb, body mass index, comorbidities, body mass index, duration of symptoms, range of motion, previous treatment to the shoulder (including surgery), and details of all treatments within the last 12 months (including the use of intra-articular therapy) (Table 1).

**Table 1 Tab1:** Schedule of study enrolment, interventions, and assessments

	Study period						
	Screening	Baseline	Treatment phase			Follow-up phase	
Timepoint	***-1 week***	***0***	***1-day***	***7-day***	***14-day***	***30-day***	***90-day***

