#### Secondary outcome

##### Functional questionnaire assessment

Participants will complete a series of patient-reported questionnaires at the preoperative, 30-day and 90-day postoperative follow-up points to assess pain, function and patient satisfaction: Oxford Shoulder Score (OSS) [23], the Constant-Murley score (CMS) [24], Pittsburgh Sleep Quality Index (PSQI) [25] and the 36-Item Short Form Survey (SF-36) [26]. In addition to the change in ASES at the terminal follow-up, ASES at other secular nodes will also be included in the secondary outcomes. All measurements will be carried out by an independent blinded assessor.

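### The blood, urine and liver tests named for assessing drug safety are scheduled only before surgery and at day 90, 76 days after the patch period ends, so laboratory changes that arise during exposure and resolve would be missed

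*Protocol article*

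**What the plan says.** Four places in the protocol article bear on this point.

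- **Purpose.** Adverse event management states: "Drug safety will be assessed by blood routine examination (BRE), urine routine test (URT), liver function tests (LFTs". The sentence goes on to further, unnamed markers of serious organ damage. A separate sentence gives ESR, ASO and RF another role, as indicators of infection in the joint.
- **Exposure.** Under Intervention, the patch is "applied around the shoulder crest immediately after surgery", and then: "The patch will be replaced with a new one every 12 h until 2 weeks postoperatively".
- **Schedule.** Table 1, under "Safety assessments", marks BRE, URT and LFTs at baseline and day 90 and at no other visit. ESR, ASO and RF have the same two marks. The adverse-event and opioid rows in that block are marked at every visit from baseline on.
- **Clinical events.** Adverse event management adds that adverse events "will be assessed and recorded at any time".

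The Methods paragraph of the abstract lists safety indicators among the secondary outcomes, and its Discussion paragraph says that safety will be evaluated. The only other mention of laboratory work, under Data collection and management, concerns routine tests before surgery.

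**The concern.** A laboratory panel adds to adverse-event reporting by showing changes that patients do not feel. For a treatment worn for two weeks, it is most informative during that period or at its end. Here the only scheduled post-baseline sample comes long after exposure has stopped.

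This has two consequences:

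- A change in blood count, urine or liver values that appears on the patch and then settles leaves no trace in the scheduled data.
- A change still present at day 90 follows 76 days without the patch, during which patients recover from surgery and may take other medicines. Linking it to the patch is then weak.

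Similar laboratory results in the two arms at day 90 would say little about safety during treatment, although the article names these tests as the means of assessing drug safety.

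**Working it through.** The point concerns timing and depends on no power or sample-size figure. The article states no interval between last patch and laboratory sample, so there is no figure to reproduce.

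**Inputs**
- Start of exposure: day 0, immediately after surgery (Intervention).
- End of exposure: day 14 (Intervention; day 14 is also the last treatment-phase column in Table 1).
- Visits: "data collected at baseline (pre-operative), 1-, 7-, 14-, 30- and 90-day postoperative" (Outcomes measurement), which match the columns of Table 1.
- Laboratory marks for BRE, URT and LFTs: baseline and day 90 (Table 1).

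**Check that the table was read correctly.** Table 1 survives here only as extracted text, so the column positions need confirming. The text places the functional questionnaires "at the preoperative, 30-day and 90-day postoperative follow-up points". Read against the seven visit columns, the OSS, CMS and SF-36 rows fall at exactly those three times. The PSQI row does not match that sentence, since the table marks it at every visit, but this is a separate matter. The adverse-event row fills all columns from baseline to day 90. The blanks in the laboratory rows are therefore real blanks and not lost marks.

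**Results**
- Gap from end of exposure to the only post-baseline sample: 90 - 14 = 76 days.
- Gap relative to the exposure period: 76 / 14 = 5.4 times.
- Treatment-phase visits (days 1, 7, 14) with a scheduled drug-safety test: 0 of 3.
- Post-baseline visits (days 1, 7, 14, 30, 90) with one: 1 of 5, the last.
- The same count for adverse events: 5 of 5.

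**Is day 14 usable?** Table 1 schedules the pressure pain threshold at day 14, and the Mechanical sensitivity section describes it as an algometer placed on the shoulder. That implies an in-person visit at which a sample could be taken.

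**The case against.** The strongest reply is that safety during treatment is covered by other means. Adverse events are collected at days 1, 7 and 14 and whenever they occur. The lidocaine effects that the article names (skin reactions, low blood pressure, dizziness, slow heart rate, gastrointestinal symptoms) would surface there and not in a blood count or liver panel. Data collection and management also calls the safety concerns minimal. All of this stands, and it limits the point to the laboratory tests. It does not remove it: the remark about minimal concern is given as the reason for having no interim analysis, and the article still names these tests as the way drug safety will be assessed.

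Several stronger readings are tempting, and the document does not support them.

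- **That the tests cannot detect harm from the exposure.** A day-90 sample can still show damage that persists. What it misses is change that resolves.
- **That the two sections contradict each other.** Adverse event management gives no times and Table 1 does, so they are compatible on their face. The problem is that the times do not suit the stated purpose.
- **That no patient will have an on-treatment value.** None is scheduled. Tests prompted by clinical need may occur, and the article does not describe them.
- **That a finding of no laboratory difference is built in.** No laboratory hypothesis or comparison is specified, so this is conjecture.
- **That ESR, ASO and RF are mistimed for the same reason.** They are listed as infection indicators. Joint infection is a complication of the operation and follow-up runs for three months, so distance from the last patch is the wrong yardstick for them.

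It could also be said that surgery itself disturbs laboratory values at day 14. Both arms undergo the same type of operation and are randomised, so a comparison between arms remains interpretable.

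**Conclusion.** The concern holds for BRE, URT and LFTs. Their only scheduled post-baseline measurement comes 76 days after a 14-day exposure, with none during or at the end of treatment. As scheduled, they describe laboratory status at day 90. They do not describe laboratory safety on the patch, and any persisting abnormality could be attributed to it only weakly.

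The weight is moderate. The primary outcome (ASES change at 90 days), the pain and opioid outcomes, and the capture of symptomatic harm are unaffected. What suffers is one component of a stated secondary outcome, and the remedy is inexpensive.

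The conclusion assumes that Table 1 is the complete laboratory schedule (no other section of the article adds a sample) and that patches stop at two weeks as written.

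**What to change.** Reconcile the stated purpose under Adverse event management with Table 1:

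- Take the post-baseline BRE, URT and LFTs at the existing day-14 end-of-treatment visit, for all patients in both arms not yet past that visit when the amendment takes effect.
- Compare change from baseline to day 14 by arm. With at most 51 patients per arm, and fewer with a day-14 value, this is best treated as descriptive.
- Leave ESR, ASO and RF as scheduled.
- Add no rule that makes a later sample depend on the day-14 result, since day-90 values would then be available only for a selected subset and could not be compared between arms.
- For patients with day-90 values only, limit any laboratory conclusion to day-90 status and make no claim about safety during treatment.

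**Cost.** The change needs a small amendment through the ethics committee and registry, the route the article already describes. If the sample is moved, the number of planned samples for these three tests is unchanged but their routine day-90 values are lost. Keeping both times avoids that loss at one extra sample per patient. Patients already past day 14 will lack the new value. The article reports recruitment under way, with the study running from May to December 2022, but does not say how many patients that is. Because the cut-off depends on calendar time and not on arm, the comparison among later patients remains a randomised one, though smaller.
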